### Secondary objectives

To assess the tolerance and adverse effects (acute and chronic) of preoperative chemoradiotherapy (CRT) in the CRT–TEM group (patient safety). To analyze postoperative morbidity and mortality in both groups (surgical outcomes). To evaluate clinical and pathological responses to CRT. To assess quality of life at 1 year after surgery in both groups. To compare long-term oncologic outcomes between groups (at 3 years): LR, DR, DFS, OS and rectal cancer–specific survival at 3 years.

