### Study procedures (Fig. 1)

**Fig. 1 Fig1:**
[figure not shown]
CONSORT trial flow chart of the TAUTEM-T1 study. CRT, chemoradiotherapy; TEM, transanal endoscopic microsurgery; TME, total mesorectal excision; MRI, magnetic resonance imaging; ER, endorectal ultrasound; FCS, full colorectal study; QoL, quality of life; CEA, carcinoembryonic antigen; CA 19–9, carbohydrate antigen 19–9; EORTC, European Organisation for Research and Treatment of Cancer; LARS, low anterior resection syndrome

Before TEM surgery or initiation of CRT, all patients will complete validated quality-of-life questionnaires from the European Organization for Research and Treatment of Cancer (EORTC) [33]: EORTC QLQ-C30 (version 2) [34] and EORTC QLQ-CR29 (colorectal cancer–specific module) [35]. Anorectal function will also be assessed using the LARS score [6, 36] and the Wexner fecal incontinence questionnaire [37].

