### Follow-up (Fig. 1)

In both groups, quality-of-life and bowel dysfunction questionnaires (EORTC QLQ-C30, EORTC QLQ-CR29, LARS, and Wexner) will be administered 12 months after surgery. For patients with a protective stoma, these assessments will be performed 12 months after stoma closure.

During the first three years, digital rectal examination and rectosigmoidoscopy with multifocal biopsies of the scar will be performed every 4 months. If any biopsy is positive for adenocarcinoma or if clinical findings are suspicious, extension studies will be completed with endorectal ultrasound (ER) and/or pelvic MRI. Tumor markers (CEA and CA 19–9) will be measured every 4 months. In addition, abdominopelvic CT and chest X-ray will be performed annually (up to 3 years). A total colonoscopy will be scheduled 1 year after surgery and, if normal, subsequent surveillance will follow each center’s institutional protocol.

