#### Secondary variables

CRT-related adverse events will be prospectively recorded and graded according to CTCAE v5.0 [47]. Acute toxicity will be collected from CRT initiation through 30 days after TEM, and late toxicity will be collected thereafter during follow-up up to 3 years.

*Quality-of-life outcomes* will be assessed using the EORTC QLQ-C30, EORTC QLQ-CR29, Wexner, and LARS questionnaires before surgery and at 12 months. Clinical response to CRT will be evaluated using the predefined multimodal clinical assessment.

*Demographic variables:* age, sex, and recruiting hospital.

*Preoperative or pre-neoadjuvant phase:* Baseline tumor characteristics will include tumor size (measured by colonoscopy, endorectal ultrasound [ER], and pelvic MRI; maximum diameter in mm), distance from the anal verge, tumor location (anterior, posterior, right or left lateral), percentage of rectal circumference involved, ER and MRI staging, presence of distant metastases (thoracoabdominal CT), preoperative tumor markers (CEA and CA 19–9), and histological grade on biopsy. After completion of neoadjuvant chemoradiotherapy and prior to local excision, clinical response will be assessed using a multimodal approach integrating digital rectal examination, endoscopy, and pelvic MRI, and will be categorized as complete, near-complete, or incomplete clinical response, according to predefined criteria.

*Surgical variables*: the technique employed, operative time, estimated blood loss, intraoperative complications, conversion to abdominal surgery, en bloc resection, and closure of the defect.

*Pathological variables*: tumor size, differentiation grade, response grade to CRT, pT stage, venous, lymphatic, or perineural invasion, tumor budding, local excision specimen margins (minimum lateral and deep distances, in mm), presence of muscularis propria, residual healthy submucosa/submucosal invasion, and sm classification according to Taulí-pT1.

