### Statistical analysis

The principal analysis, from which the main study conclusions will be derived, will follow the intention-to-treat (ITT) approach, including all randomized patients. A per-protocol (PP) analysis will also be conducted, including patients from both groups who do not meet withdrawal criteria and who complete the study protocol. Losses to follow-up and their potential impact on outcomes will be analyzed. Pre-specified sensitivity analyses will assess the impact of missing primary endpoint data.

Quantitative variables will be described using mean and standard deviation or, when appropriate (based on the Kolmogorov–Smirnov or Shapiro–Wilk normality tests), median, interquartile range, and range. Categorical variables will be summarized as absolute numbers and percentages.

Comparisons between groups for quantitative variables will be performed using the Student’s t-test (when assumptions of normality and homoscedasticity are met); otherwise, the Mann–Whitney U test will be applied. Categorical variables will be compared using Pearson’s χ^2^ test or Fisher’s exact test, as appropriate.

Survival analyses (local recurrence, distant recurrence, and mortality) will be performed using Kaplan–Meier estimates and compared with the log-rank test.

In addition, an exploratory DFS analysis will be performed stratifying patients according to adverse histopathologic features identified in the local excision (TEM) specimen (e.g., lymphovascular invasion, poor differentiation, tumor budding, and depth of submucosal invasion), and results will be interpreted as hypothesis-generating due to limited power for subgroup analyses.

Statistical significance will be set at *p* < 0.05. When applicable, results will be presented with their 95% confidence intervals (95% CI).

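### The only stated test for the 12-month quality-of-life and bowel-function scores ignores the baseline scores already collected; baseline adjustment would be more precise at no data cost

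*Protocol article*

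**What the plan says.** The Statistical analysis section of the Protocol article states a single rule for continuous outcomes: "Comparisons between groups for quantitative variables will be performed using the" Student's t-test when normality and equal variances hold; "otherwise, the Mann–Whitney U test will be applied". It names no covariate, regression model or change score for such outcomes, and it does not mention the questionnaires by name.

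The questionnaires are planned at two times.

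- **Baseline.** Study procedures (Fig. 1): "Before TEM surgery or initiation of CRT, all patients will complete validated quality-of-life questionnaires" (QLQ-C30 and QLQ-CR29). Of bowel function it says: "Anorectal function will also be assessed using the LARS score", together with the Wexner questionnaire.
- **12 months.** Follow-up (Fig. 1) says that the same four instruments "will be administered 12 months after surgery", or 12 months after closure for patients with a protective stoma.
- **Summary.** Secondary variables lists the "EORTC QLQ-C30, EORTC QLQ-CR29, Wexner, and LARS questionnaires before surgery and at 12 months". The Discussion also describes assessment at baseline and at 12 months.

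The Secondary objectives include: "To assess quality of life at 1 year after surgery in both groups".

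**The concern.** These scores carry weight in the trial's conclusion. The Hypothesis section expects better rectal preservation without harm to quality of life, and the abstract's conclusion extends this to bowel function. The Discussion accepts that pelvic chemoradiotherapy may impair anorectal function and so offset the gain from keeping the rectum. It gives this as the reason for measuring function and quality of life.

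For a claim of no harm, imprecision is not neutral: a wide interval or a non-significant test is easily read as reassurance. The sample size is set by the primary endpoint alone, so precision on the questionnaires depends on how they are analysed. A test of the 12-month scores alone leaves in the error term all the between-patient variation that the baseline score could explain.

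A second, smaller matter is that the t-test compares means while Mann–Whitney compares orderings. The effect being estimated could therefore differ from scale to scale, depending on the observed data.

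**Working it through.** **The plan's own figure.** The article gives no standard deviation, effect size or power for the questionnaires. Its only sample size is for the primary endpoint (Sample size section): 0.60 against 0.85, two-sided α = 0.05, 80% power, 10% dropout. With unpooled variance:

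n = (1.960 + 0.842)² × (0.60 × 0.40 + 0.85 × 0.15) / 0.25² = 7.849 × 0.3675 / 0.0625 = 46.2, so 47 per group.

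47 / 0.90 = 52.2, so 53 per group and 106 in total. The stated total is reproduced, but it says nothing about the questionnaires.

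**Inputs for the questionnaire comparison**

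- Patients per arm with a 12-month score: 53 × 0.90 = 47.7, taken as 48.
- Correlation r between baseline and 12-month score: not in the article. Assumed 0.3, 0.5 and 0.7, with 0 as the worst case.
- True difference for the power figures: assumed 0.5 SD.

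**Formulas**

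- Variance of the adjusted comparison relative to the unadjusted one: 1 − r².
- With the small-sample cost of estimating the slope: (1 − r²) × [1 + 1/(2n − 4)]. At n = 48 the bracket is 1 + 1/92 = 1.011.
- Equivalent number per arm under an unadjusted test: n / (1 − r²).
- Difference detectable with 80% power: 2.802 × √(2/48) × √(1 − r²) = 0.572 × √(1 − r²), in SD units.
- Power at 0.5 SD (normal approximation): Φ(0.5 / [√(2/48) × √V] − 1.960), where V is the variance ratio with the small-sample cost, and V = 1 for the unadjusted test.

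**Results, 48 per arm**

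| r | 1 − r² | With small-sample cost | Equivalent n per arm | Detectable difference (SD) | Power at 0.5 SD |
|---|---|---|---|---|---|
| Unadjusted t-test | 1 | 1 | 48 | 0.57 | 0.69 |
| 0 | 1.00 | 1.01 | 48 | 0.57 | 0.68 |
| 0.3 | 0.91 | 0.92 | 53 | 0.55 | 0.72 |
| 0.5 | 0.75 | 0.76 | 64 | 0.50 | 0.80 |
| 0.7 | 0.51 | 0.52 | 94 | 0.41 | 0.93 |

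**Check by simulation.** In 6,000 simulated trials with normal data, 48 per arm, r = 0.5 and a 0.5 SD difference, power was 0.67 for the t-test, 0.64 for Mann–Whitney and 0.78 for the adjusted model. The simulated variance ratios were 1.01, 0.92, 0.75 and 0.52 for r = 0, 0.3, 0.5 and 0.7, in agreement with the table.

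**If change scores were meant.** The article does not say so. Their variance relative to the 12-month score alone is 2(1 − r), assuming equal variances at the two times: 1.4, 1.0 and 0.6 for r = 0.3, 0.5 and 0.7. The adjusted model's 0.91, 0.75 and 0.51 are lower in each case.

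**The case against.** **The rule is generic.** It covers everything from operative time to length of stay, and it does not name the questionnaires. A fuller model may stand in an analysis plan that is not shown. This stands as a limit: the rule reaches these scores only by default, because they are quantitative and no other method is given. It is nonetheless the method the article states. If LARS were analysed in categories, the stated χ² or Fisher test would apply. Those tests are also unadjusted, but the variance formula does not carry over to them directly.

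**The tests are valid.** A reader might infer that chance baseline imbalance biases the comparison. It does not: under randomisation, such imbalance is already allowed for in the error rate and the confidence interval. Only efficiency is at stake.

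**The gain is assumed.** Surgery, chemoradiotherapy in one arm and completion TME in some patients come between the two measurements, and patients with a stoma are assessed later. All of this could weaken r. At r = 0.3 power rises only from 0.69 to 0.72. This stands, and it is why a range is given. The downside at r = 0 is about 1% in variance.

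**Baseline timing.** Secondary variables says "questionnaires before surgery and at 12 months", and a reader might infer that the CRT–TEM arm could have a baseline taken after chemoradiotherapy, which would hide its harm. The article does not support this. Study procedures places the baseline before TEM or before CRT starts, and a score taken then is also a score taken before surgery. Moreover, a test of 12-month scores alone would not use the baseline at all. What remains is a wording alignment, which becomes useful once the baseline score is a covariate.

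**Normality pre-test.** A reader might also infer that a formal normality test selects the comparison test. Kolmogorov–Smirnov and Shapiro–Wilk are named only for choosing descriptive summaries. For comparisons the article says only that the assumptions must be met.

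**Conclusion.** The point holds as a precision improvement for secondary endpoints. The one stated method for quantitative comparisons is unadjusted and by default covers the quality-of-life and bowel-function scores, although their baseline values are collected. For an assumed r of 0.3 to 0.7, adjustment cuts variance by about 9% to 49% (8% to 48% after the small-sample cost at 48 per arm). At r = 0.5 this is worth about 64 patients per arm instead of 48. The size of the gain rests on that assumed correlation and on a linear model for the scores. The stated tests are not wrong, and the primary analysis and the total of 106 do not change. Because these scores support the claim that organ preservation does not come at the cost of function, the change is worth making.

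**What to change.** In Statistical analysis, add that each 12-month questionnaire score will be analysed with a linear model containing treatment arm and the baseline score of the same scale, reporting the adjusted mean difference with its 95% CI. Robust or bootstrap standard errors would be used if residuals are skewed. State that this replaces the assumption-dependent choice between t-test and Mann–Whitney for these endpoints.

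In Secondary variables, repeat the timing already given under Study procedures: baseline is before CRT initiation in the CRT–TEM arm and before surgery in the TEM arm.

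The cost is one or two sentences in each section and one degree of freedom per model, with no new visits, data or patients. The change should be made before outcome data are seen.

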## Discussion

Management of cT1N0M0 rectal adenocarcinoma remains heterogeneous and challenging, largely because adverse pathological features cannot be reliably identified preoperatively [48]. Endoscopic biopsy confirms invasive adenocarcinoma but does not provide the key risk factors required for definitive stratification, and cross-sectional imaging frequently categorizes these tumors at the T1–T2 interface with N0 status. Importantly, even in the absence of adverse features, long-term local recurrence (LR) after local excision may exceed the rates observed in our TAUTEM arm of T2–T3abN0M0 treated with neoadjuvant therapy plus TEM [22]. These limitations support an upfront strategy based on clinical staging (cT1N0M0) rather than postoperative pathology.

Against this background, TAUTEM-T1 will test whether preoperative chemoradiotherapy followed by transanal endoscopic surgery (CRT–TEM) reduces LR, avoids completion TME triggered by adverse pathology, and—crucially—increases rectal preservation without compromising oncologic safety. The trial is designed to balance the risks of overtreatment (administering CRT to patients who may do well with TEM alone) and undertreatment (exposing patients to completion or salvage TME in case of recurrence). By enrolling patients at the cT1N0M0 decision point, the protocol aligns with real-world clinical workflow.

Nevertheless, this strategy entails a clear trade-off: delivering pelvic CRT upfront in cT1N0M0 disease may overtreat a proportion of patients and can lead to acute and late pelvic toxicity. Moreover, pelvic irradiation may reduce the feasibility of using radiotherapy as a salvage option in the event of local recurrence and may complicate or preclude curative radiotherapy for other pelvic malignancies arising later in life (e.g., prostate or gynecologic cancers). In this context, short-term feasibility and safety of the same long-course CRT regimen have been previously shown in the TAU-TEM randomized trial, with high treatment compliance and no grade 4–5 CRT-related toxicity [49]. These long-term implications are part of the ethical rationale for this randomized trial and will be carefully monitored through systematic recording of acute and chronic CRT-related adverse events.

Pelvic CRT may impair bowel/anorectal function (e.g., urgency, frequency, incontinence and LARS), potentially offsetting organ-preservation benefits; therefore, function and QoL will be prospectively assessed using validated questionnaires (EORTC QLQ-C30/CR29, LARS and Wexner) at baseline and at 12 months (or 12 months after stoma closure).

Two alternative strategies may also be considered in cT1N0M0 disease. First, local excision with adjuvant (chemo)radiotherapy reserved for unfavorable pathology could reduce upfront CRT exposure; however, published evidence of (chemo)radiotherapy after local excision is associated with higher local recurrence rates than completion TME, particularly in pT1-2N0 disease, and may therefore represent a suboptimal rescue pathway when occult ≥ pT2 is identified [50, 51]. Second, a response-adapted approach randomizing complete/near-complete responders after CRT to watch-and-wait versus local excision is clinically appealing but requires robust evidence on pathological complete response rates and the safety of deferring surgery in cT1N0M0 tumors. TAUTEM-T1 is designed to generate this foundational evidence under standardized full-thickness excision and pathology review; if a high pCR rate and durable organ preservation are confirmed, a subsequent trial incorporating a watch-and-wait strategy in selected responders would be justified.

To our knowledge, no phase III multicenter randomized trial has specifically compared neoadjuvant therapy plus local excision versus standard TEM in T1N0M0 rectal cancer. Although earlier phase II studies in broader stages reported feasibility of organ preservation after neoadjuvant therapy, they did not focus on T1 disease and did not include a dedicated TEM comparator arm [52]. TAUTEM-T1 addresses this evidence gap using a superiority design and a patient-centered primary endpoint (rectal preservation), closely linked to functional outcomes and quality of life.

Methodologically, compare with the previous TAUTEM study [22, 24], the protocol incorporates current practice refinements: clinical response assessment around week 9 post-CRT and local excision at week 10 [53, 54]; standardized morbidity capture at 30 and 60 days using both Clavien–Dindo and the Comprehensive Complication Index [55]; centralized pathological review (including the Taulí-pT1 classification); and ITT-based inference with a planned interim analysis. These features enhance internal validity and the interpretability of functional outcomes alongside oncologic endpoints.

This trial could form the foundation for selecting cT1N0M0 patients with frequent complete clinical response for a future watch-and-wait strategy, contingent on confirmation of a high pathological complete response rate with local excision. Economically, the organ-preservation strategy is expected to reduce complex surgeries, hospital stays, stoma care requirements, and associated costs, thereby improving patient quality of life and healthcare resource efficiency.

Limitations include the logistical complexity of a 15-hospital multicenter trial; however, the majority of these centers participated in the original TAUTEM study, which supports homogeneity and high-quality trial execution. Recruitment timelines may be limited by these logistics, yet the smaller sample size relative to TAUTEM may mitigate delays. The superiority design allows an interim analysis with the possibility of early stopping for confirmed benefit, and methodological rigor is reinforced by centralized review. Although the Taulí-pT1 classification is relatively novel, its validated use and pathology support from Parc Taulí Hospital encourage broader adoption [11, 13]. Finally, selecting rectal preservation as the primary endpoint—clinically meaningful and closely linked to oncologic safety and quality of life—highlights the trial’s translational relevance. If positive, TAUTEM-T1 may help standardize stage I rectal cancer management around neoadjuvant therapy and local excision, reducing practice variability while optimizing oncologic, functional, and quality-of-life outcomes.

## Conclusion

This study aims to increase the rate of rectal preservation in cT1N0M0 rectal cancer through preoperative chemoradiotherapy (CRT) combined with local surgery (TEM), thereby improving oncologic outcomes—local recurrence, overall survival, and disease-free survival—as well as quality of life and bowel function.

## Data Availability

The datasets generated and/or analyzed during the current study will be made available in the Dataverse repository of the Institut d’Investigació i Innovació Parc Taulí (I3PT), the institution to which the corresponding author is affiliated. The data will be accessible upon publication.
